**Figure 2 F2:**
[figure not shown]
Location of auricular acupoints.

The intervention group will also accept MA at *Zusanli* (ST36), *Shangjuxu* (ST37), *Xiajuxu* (ST39), *Hegu* (LI4), and *Taichong* (LR3) according to *Acupuncture and Moxibustion* (23) (Table 3 and Figure 3). A single-use stainless steel needle (0.25 mm × 40 mm) (Suzhou Medical Products Factory Co., Ltd., Suzhou, China) will be used, and Deqi sensation (a sensation of sourness, numbness, or distension) should be achieved during the process. The needle should be retained for 20 min and then withdrawn quickly. Patients will receive MA once a day for consecutive days after surgery until the first defecation after surgery.

**Table 3 T3:** Location of acupoints.

Acupoints	Locations
Zusanli (ST36)	On the lateral aspect of the leg, 3 cun inferior to Dubi (ST35), on the line connecting Dubi^a^ (ST35) and Jiexi^b^ (ST41)
Shangjuxu (ST37)	On the lateral aspect of the leg, 6 cun inferior to Dubi (ST35), on the line connecting Dubi(ST35) and Jiexi(ST41)
Xiajuxu (ST39)	On the lateral aspect of the leg, 9 cun inferior to Dubi (ST35), on the line connecting Dubi (ST35) and Jiexi (ST41)
Hegu (LI4)	On the dorsum of the hand, radial to the midpoint of the second metacarpal bone
Taichong (LR3)	On the dorsum of the foot, between the first and second metatarsal bones, in the depression anterior to the junction of the bases of the two bones, or over the dorsalis pedis artery

^a^
Dubi (ST35): On the anterior aspect of the knee, in the depression lateral to the patellar ligament.

^b^
Jiexi (ST41): On the anterior region of the ankle, in the depression at the center of the front surface of the ankle, between the extensor halluces longus tendon and the extensor digitorum longus tendon.

**Figure 3 F3:**
[figure not shown]
Location of acupoints.

### Control group: ERAS

The control group will receive regular treatment of ERAS 3 days before surgery because patients are always admitted to the hospital several days earlier for standard preoperative blood testing and bowel preparation, including taking oral anti-inflammatory drugs, having liquid food 72 h before the operation, accepting enema 24 h before the operation, using intravenous antibiotics to preventing infection, and so on. In addition, the control group will be initiated on a liquid diet within 24 h after surgery to stimulate bowel movement.

Patients in both groups will receive the same postoperative procedures in mobilization to avoid bias in evaluating the onset of POI, including getting out of bed within 24 h after surgery and walking three times a day for a distance of 50–100 m after 48 h.

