**Methods:**

This is a single-center, assessor-blinded, randomized controlled trial. A total of 160 participants are supposed to recruit at Shanghai Tenth People's Hospital and randomly divided into two parallel groups in a 1:1 ratio. The intervention group are planned to receive manual acupuncture combined with auricular acupressure, while the control group are planned to receive regular enhanced recovery after surgery treatment. The primary outcome is the time to first defecation and first flatus after surgery. The secondary outcomes include the length of postoperative hospital stay, intensity of postoperative abdominal pain and distension, severity of postoperative nausea and vomiting, time to tolerate diet, inflammatory index, and incidence of prolonged postoperative ileus.

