## Interventions

### Intervention group: MA combined with AA

MA and auricular acupressure procedures of the intervention group will be administered by licensed acupuncturists with 5–12 years of education in acupuncture and at least 3 years of clinical experience. They will all undergo unified and standardized training before trial initiation.

The intervention group will accept AA at the small intestine (CO6), large intestine (CO7), abdomen (AH8), and sub-cortex (AT4) according to the *Nomenclature and Location of Auricular Points* (Table 2 and Figure 2). Vaccaria seeds (Wang-Bu-Liu-Xing) (40 mm × 40 mm) (Changshu Shenling Medical Products Factory Co., Ltd., Changshu, China) will be embedded on the surface of auricular points and maintained between the two treatments. Two ears will accept AA alternately once daily. Participants will be suggested to press each point gently for 1 min thrice daily. The treatment will start 3 days before elective laparoscopic surgery and continue until the first defecation after surgery.

**Table 2 T2:** Location of auricular acupoints.

Auricular acupoints	Locations
Small intestine (CO6)	At the intermediate 1/3 of the region between the helix crus and Line AB^a^
Large intestine (CO7)	At the anterior 1/3 of the region between the helix crus and Line AB
Abdomen (AH8)	On the upper 2/5 of the body of the antihelix crus
Sub-cortex (AT4)	On the medial side of the antitragus

Point A: At the medial edge of the helix at the junction between the middle and upper 1/3 of the line from the notch of the helix crus and the inferior edge of the inferior antihelix crus. Point B: At the junction of the middle and posterior 1/3 of the line extending from the end of the helix crus to Point D. Point D: At a level line drawn from the end of the helix crus crossing the concha edge of the antihelix.

^a^
Line AB: A curved line that extends from Point A to Point B and mirrors the inferior edge of the helix crus.

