#### Time to tolerate diet (liquid or semi-liquid food)

Postoperative ileus can result in delays in time to mobilization and resumption of oral intake, which may further affect patient's satisfaction and wound recovery (31). Therefore, the time to tolerate diet will be recorded as a reference.

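### As written, the early postoperative liquid diet goes to the control group only, so a bowel-directed co-intervention differs between arms and, on the protocol's own rationale, biases against acupuncture plus auricular acupressure

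*Protocol article*

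**What the plan says.** All references are to the protocol article.

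- **Control group: ERAS, first paragraph.** The control group gets regular ERAS care starting 3 days before surgery. The paragraph then adds a postoperative item: "In addition, the control group will be initiated on a liquid diet" within 24 h "after surgery to stimulate bowel movement".
- **Same section, second paragraph.** This is the only statement of care common to the arms: "Patients in both groups will receive the same postoperative procedures in mobilization to avoid bias". The details that follow concern leaving bed and walking. Diet is not mentioned.
- **Intervention group: MA combined with AA.** "The intervention group will accept AA at the small intestine" and other auricular points, and "The intervention group will also accept MA at" five body points. The section names no ERAS element, diet or usual care.
- **Abstract, Methods.** The intervention arm receives MA+AA, "while the control group are planned to receive regular enhanced recovery after surgery treatment". The Discussion likewise presents ERAS as the comparator and refers to two treatments.
- **Outcomes.** The primary outcomes are the times to first defecation and first flatus. Time to tolerate liquid or semi-liquid food is secondary: "Therefore, the time to tolerate diet will be recorded as a reference".

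**The concern.** The diet sentence names one arm, concerns the postoperative period, and states as its purpose the function that the primary outcomes measure. The next paragraph shows that the authors knew unequal postoperative care would bias the comparison, yet they equalised mobilization alone.

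If staff follow the text, the arms differ in MA+AA and also in early feeding. The between-arm difference then mixes the two. For time to tolerate diet the problem is more direct: a start of feeding fixed for one arm and left open for the other partly determines the outcome.

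**Working it through.** **Step 1. Who receives what, as written**

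| Care element | Control | Intervention |
|---|---|---|
| MA+AA | no | yes |
| Preoperative ERAS items | yes | not stated, probably shared |
| Liquid diet within 24 h after surgery | yes | not stated |
| Mobilization after surgery | yes | yes |

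Preoperative care is probably shared because the text explains it by hospital routine: "because patients are always admitted to the hospital several days earlier for standard preoperative blood testing and bowel preparation". The diet sentence carries no such explanation.

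**Step 2. Direction of the bias**

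Let Δ be the true hours by which MA+AA shortens time to first defecation, and δ the hours by which a control-only diet shortens it. The expected observed difference is Δ − δ. On the protocol's rationale δ > 0, so the observed difference is too small by δ. If Δ = 0, the expected difference is −δ, which favours control. The diet therefore cannot create a false advantage for MA+AA on defecation. The same reasoning holds for flatus. It applies to the diet alone; I claim no direction for the preoperative items.

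**Step 3. The plan's own sample size**

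Inputs from Sample size calculation: 77.8 (SD 15.6) h against 85.1 (SD 13.35) h, two-sided α 0.05, power 0.80, 1:1 allocation.

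- Difference: 85.1 − 77.8 = 7.3 h.
- Normal approximation: n per arm = 2 × SD² × (1.960 + 0.842)² / 7.3².
- With SD 15.6: 71.7, so 72, as stated. Then 72 / 0.9 = 80 per arm.
- With pooled SD √((15.6² + 13.35²)/2) = 14.52: 62.1, so 63, which does not match.

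The planned 72 therefore corresponds to the larger SD.

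**Step 4. Hypothetical illustration**

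The documents give no value for δ, so 1 to 3 h is purely an assumption. Take Δ = 7.3 h, 72 per arm and a two-sided t-test with 142 df. The standard error is SD × √(2/72), which is 2.60 h with SD 15.6 and 2.42 h with SD 14.52.

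| Assumed δ (h) | Δ − δ (h) | Power, SD 15.6 | Power, SD 14.52 |
|---|---|---|---|
| 0 | 7.3 | 0.796 | 0.850 |
| 1 | 6.3 | 0.672 | 0.734 |
| 2 | 5.3 | 0.526 | 0.585 |
| 3 | 4.3 | 0.376 | 0.423 |

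The choice of SD moves the level but not the pattern. The table applies only if the arms are fed differently in the trial and the pilot's 7.3 h came from arms fed alike. If the pilot had the same imbalance, δ is already inside the 7.3 h and no power is lost, though the 7.3 h would then not be the effect of MA+AA alone.

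**The case against.** The strongest reply is that ERAS is meant as background care for everyone and the sentence is loosely drafted under a control-group heading. Several things support this. The care is called regular and tied to what patients at this hospital are always admitted for. The Background describes ERAS as covering the whole perioperative period. The Discussion bases the treatment on ERAS thinking. No reason is given anywhere for withholding early feeding from the intervention arm. Study design also refers to Figure 1 and Table 1 for details; the figure is not available here and the AA + MA and ERAS rows of the table show no readable marks. Finally, the preoperative sentence also has the control group as its subject, so naming one arm does not by itself prove exclusivity.

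This stands as a reason for doubt about what is done at the bedside. A reader might infer that the intervention arm is in fact denied ERAS or early feeding; the documents do not establish that. The reply does not repair the wording, however. An explicit assignment to one arm, followed by a statement of equal care limited to mobilization, is wrong if feeding is shared and confounding if it is not.

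A second objection also stands. A reader might infer that any MA+AA advantage would be uninterpretable. By Step 2, a significant advantage on defecation or flatus would have arisen despite the diet difference. The difficulty lies with null or reduced results, the size of the effect, and time to tolerate diet.

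**Conclusion.** The point holds as a defect in the stated rule. Read literally, the article gives early feeding intended to stimulate the bowel to the control arm only. That biases the primary comparison against MA+AA, leaves a null or reduced difference uninterpretable, distorts the effect size, and confounds time to tolerate diet.

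The direction rests on the protocol's own claim that the diet promotes bowel movement. The size is unknown. It would be tempting to read Step 4 as showing that the trial is underpowered by a known amount, but its shifts have no source in the documents, and the loss is nil if both arms are fed alike or the pilot had the same imbalance. Confidence is medium, because shared ERAS care is a plausible intent. The text should be corrected either way.

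**What to change.** In Intervention group: MA combined with AA and in Control group: ERAS, state that both arms receive the identical ERAS pathway, including the liquid diet within 24 h after surgery, and that MA+AA is added in the intervention arm. Align the Abstract's Methods and the Discussion with this add-on design.

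Trial status says that recruitment is under way, so also check first-feeding time by arm from routine charts. If it differed, report it and limit the conclusion to a comparison of two care packages.

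The cost is one sentence in each intervention section, matching edits in two other places, and a chart check. No extra patients, visits or procedures are needed.

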## Outcome measures

### Primary outcome measures

The primary outcomes are the time to first defecation and first flatus, which is regarded as a bowel function indicator. This time is calculated from the end of laparoscopic surgery and will be recorded by nurses with accuracy to the hour.

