## Sample size calculation

Our primary outcome is the time to first defecation. The unpublished experimental data on the effects of AA combined with MA, based on a 2-week prior pilot experiment, were used for the sample size calculation. The time to first defecation is 77.8 ± 15.6 h in the intervention group and 85.1 ± 13.35 h in the control group. We chose the two-sample *t*-test model with a two-tailed test, and the relevant calculating parameters are a significance level of 0.05, a power of 0.80, and an allocation ratio of 1:1. The required number of participants per group is 72. Considering a dropout rate of 10%, the sample size for this trial is 80. Thus, a total of 160 participants will be recruited.

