## Statistical analysis

The principle of intention-to-treat (ITT) analysis will be followed in the process of statistical analysis. The last observation carried forward (LOCF) analysis will be applied for missing data in ITT analysis. Supplementary per-protocol analysis will also be carried out. All the statistical analyses will be performed using SPSS Ver. 24.0 with a significance level of 0.05.

First, the different baseline characteristics of the two groups will be described, and data will be presented as mean or median with standard deviation or interquartile range for continuous variables and as frequency distributions for categorical variables. Moreover, the histograms, boxes, and other representations will also be considered for the graphic analysis of corresponding data. A two-sample *t*-test for quantitative data or a chi-squared test for qualitative data will be performed as a homogeneity test, and the covariance analysis will also be performed if an adjustment is needed for a baseline characteristic.

Second, the analyses will focus on whether statistically better treatment outcomes could be achieved in the intervention group. *P*-values less than 0.05 will be considered statistically significant, and tests will be two-sided.

In terms of the changes in the measurement data, the two-sample *t*-test or the Wilcoxon rank-sum test will be used to compare the two groups and to determine differences according to normality. The mean change and the interaction between groups and observed time frames will be analyzed using a two-factor repeated measure analysis. If necessary, a mixed model approach will also be used.

Finally, safety analysis will be performed using the chi-squared test or Fisher's exact test based on the frequency and percentage of all recorded adverse events between the two groups.

The above plan is what we intend to do; however, the final analyses reported may differ from those planned, allowing for *post-hoc* analysis where it is indicated.

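### The article contradicts itself on the primary outcome: two outcomes in the abstract and outcome section, first defecation alone in the sample size section

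*Protocol article*

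**What the plan says.** The article states its primary outcome in three places.

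- Abstract, Methods: "The primary outcome is the time to first defecation and first flatus after surgery". Two events appear under a singular noun.
- Primary outcome measures: "The primary outcomes are the time to first defecation and first flatus, which is regarded as a bowel function indicator". Here the noun is plural.
- Sample size calculation: "Our primary outcome is the time to first defecation". Flatus is not mentioned.

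The planning figures concern defecation only: "The time to first defecation is 77.8 ± 15.6 h in the intervention group and 85.1 ± 13.35 h in the control group". The test and error rates are given by "We chose the two-sample *t*-test model with a two-tailed test" and "a significance level of 0.05, a power of 0.80, and an allocation ratio of 1:1", with the result "The required number of participants per group is 72", raised to 80 per group for 10% dropout.

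The statistical analysis section sets a single threshold for all comparisons: P-values "less than 0.05 will be considered statistically significant, and tests will be two-sided". It also reserves the right to report analyses other than those planned.

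**The concern.** A reader cannot tell from the article whether the trial has one primary outcome or two, or, if two, what would count as success. Suppose first defecation gave p = 0.20 and first flatus p = 0.03. Under the sample size section the trial has failed on its primary outcome. Under the outcome section it could be reported as positive on one of its primary outcomes. Both reports could cite the published article.

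Two things are at stake. The first is the type I error rate, if a significant result on either outcome is allowed to carry the conclusion while each is tested at 0.05. The second is power, if both outcomes must be significant, because the calculation covers only one of them.

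**Working it through.** **Inputs.** From the sample size section: means 77.8 h and 85.1 h (difference 7.3 h), SDs 15.6 h and 13.35 h, two-sided alpha 0.05, power 0.80, 72 per group, 10% dropout. From the statistical analysis section: two-sided 0.05 for every test. Assumed, because the documents do not give it: the correlation ρ between the two test statistics, varied from 0 to 0.9.

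**1. The plan's own figure.** n per group = 2(z₀.₉₇₅ + z₀.₈₀)² × SD² / difference² = 2 × (1.960 + 0.842)² × 15.6² / 7.3² = 71.7, so 72. The larger (intervention) SD is needed to reach this; the exact t calculation gives 73. The pooled SD, √[(15.6² + 13.35²)/2] = 14.52 h, gives only 63 (normal) or 64 (t). Dropout: 72 / 0.90 = 80. So the 72 is reproduced, for first defecation alone.

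**2. Error rate if either outcome may carry success.** The chance of at least one false positive is 1 − P(|Z₁| < 1.96, |Z₂| < 1.96), with (Z₁, Z₂) bivariate normal. At ρ = 0 this is 1 − 0.95² = 0.0975.

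| ρ (assumed) | At least one false positive, two-sided | Of which in favour of the intervention |
|---|---|---|
| 0 | 0.0975 | 0.049 |
| 0.5 | 0.091 | 0.045 |
| 0.8 | 0.078 | 0.039 |
| 0.9 | 0.070 | 0.035 |

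The nominal values are 0.05 and 0.025. The excess disappears only at ρ = 1. Two measures of bowel recovery in the same patient are probably positively correlated, so 7% to 9% is more realistic than the full 9.75%.

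**3. Power if both outcomes must succeed.** Each test stays at 0.05 and the error rate is not inflated. With 72 per group and SD 15.6, the standardised shift is 7.3 / (15.6 × √(2/72)) = 7.3 / 2.6 = 2.81, so power for defecation alone is Φ(2.81 − 1.96) = 0.80. If flatus had the same standardised effect (an assumption; no flatus figures are given), joint power would be 0.80² ≈ 0.64 at ρ = 0, 0.69 at 0.5, 0.73 at 0.8 and 0.75 at 0.9. With the pooled SD the range is 0.73 to 0.81.

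**4. Cost of splitting alpha instead.** At 0.025 for each outcome and SD 15.6, power for defecation with 72 per group is Φ(2.81 − 2.24) ≈ 0.71. Restoring 0.80 takes 87 (normal) or 89 (t) per group, which is 97 or 99 after dropout.

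**5. Single primary outcome.** Alpha stays at 0.05 and n stays at 72, or 80 with dropout.

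**The case against.** The strongest reply is that no error inflation has been shown. Nothing in the article says that one significant outcome is enough. The abstract's singular noun could mean that both events are to be read together, and if the sample size section governs there is only one primary outcome. A reader might infer that the plan tests two primaries on an either-or basis with a family-wise error near 10%. The documents do not support that as a statement of fact; the 7% to 9.75% is conditional on a rule that the text leaves open. This part of the objection stands.

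A second reply is that testing order and alpha splits are commonly left to a statistical analysis plan, which is not shown. That also stands, so the absence of a multiplicity rule is not charged here as an omission. It does not remove the contradiction, because the article itself names the primary outcome three times and disagrees with itself.

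Two further inferences should be resisted.

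- A reader might hold that flatus is the weaker measure, more open to bias because participants are unblinded. The article describes one process for both outcomes, recording by nurses to the hour, and does not say whether those nurses are blinded. It gives no basis for ranking one outcome below the other.
- A reader might quote 77% power for defecation under an alpha split with 72 per group and set it against the planned 80%. That figure uses the pooled SD, under which 72 per group already has about 85% power at 0.05; with 80 per group analysed it would be about 82% at 0.025. On the SD that reproduces 72, the figure is about 71%.

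Finally, a single primary is not the only coherent repair. Requiring both outcomes, or splitting alpha with a matching sample size, would also be valid.

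**Conclusion.** The contradiction is established from current text and does not depend on any calculation: the abstract and the outcome section name two primary outcomes, while the sample size section names one and sizes the trial on it. It matters because the choice can reverse the trial's stated conclusion.

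The size of the consequence depends on which reading is adopted. Under an either-outcome rule, the family-wise error is about 7% to 9.75% for assumed correlations of 0.9 down to 0. Under a both-outcomes rule there is no inflation, but the joint power is unplanned; the figures in the working are illustrative, since they assume that flatus has the same standardised effect as defecation. With first defecation as the sole primary outcome, the stated alpha, power and sample size all hold together. That is the only one of the three readings that the sample size section supports as written.

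**What to change.** In the abstract and in the section on primary outcome measures, name time to first defecation as the single primary outcome, as the sample size section already does. List time to first flatus as the first secondary outcome, and state that it is tested at two-sided 0.05 only if first defecation is significant. This fixed order holds the error rate across the two outcomes at 0.05.

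The change is one of wording. The 72 per group, the 80 after dropout and the power for defecation are unaffected. The registry record was not seen; if it lists both outcomes as primary, it needs the same amendment. The article reports that recruitment is under way, so the change should be made and dated before any comparison of outcomes by group.

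The downside is that a significant result on flatus alone could not support a confirmatory claim. If the investigators want flatus to carry such a claim, they should keep both outcomes as primary, state the success rule, and redo the sample size with stated assumptions for flatus.
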